### 1.3. Main hypotheses

The following are the principal hypotheses of the study, and the numbering of the hypotheses is linked to the numbering of the objectives (e.g., H1.1 designates the hypothesis linked to the objective O1.1, Hbase designates the hypothesis at baseline, i.e., before randomization and the experimental procedure).

(H1.1) (a) Measures pertaining to S-ART will be significantly higher in SPs who receive MT compared to those who receive RT and thus, at post-training and at follow-up. The only measure that we hypothesize to be equally lower for both groups (at both time points) is stress. (b) Within-groups effects (i.e., among the three time points) will be significant for all the outcomes for the MT group, and only for stress for RT.

(H1.2) (a) The effects of MT on S-ART measures will be moderated by the adherence of the SPs to the practice at both time points (i.e., post-training and follow-up). (b) The effects of RT on stress will be moderated by the SPs’ adherence to practice.

(H2.1) (a) Objective and subjective measures pertaining to the quality of the SP-SR interactions will be significantly higher in dyads with a SP who received MT compared to dyads with a SP who received RT at both time points (i.e., post-training and follow-up). (b) Within-groups effects (across time) will be only significant for the dyads with an SP who received MT.

(H2.2) The effects of MT of the SPs on the quality of SP-SR interactions (measured subjectively and objectively) will be mediated by the increase on S-ART of the SPs at both times points (i.e., post-training and follow-up).

(H3.1) SRs who interacted with SPs who received MT training will show significantly (a) higher positive emotional states, lower negative emotional states and (b) higher mindfulness states following their interaction compared to those who interacted with SPs who received RT and thus, at both time points (i.e., post-training and follow-up). (c) Within-groups effects will be only significant for the SR who interacted with an SP with MT training.

(H3.2) The effects of MT of the SP on the emotional and mindfulness states of the SR will be mediated by the increase in the quality of the SP-SR interaction and moderated by SRs’ Fears of Compassion from Others (i.e., higher fears of compassion will reduce the mediation effects) at both time points (i.e., post-training and follow-up).

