(Hbase) (a) At baseline, the S-ART measures of the SPs will be associated with the quality of SP-SR interactions (as measured objectively and subjectively) and with the emotional and mindful state of the SR and (b) the association between the S-ART of the SPs and the emotional/mindful states of the SR will be mediated by the quality of SP-SR interactions and moderated by Fears of Compassion from Others.

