## 2. Methods and design

### 2.1. Participants

We aim to recruit 640 adult community members (18–35 years old, 50% female) through advertising on social media. The sample size was based on detecting significant differences among the groups (i.e., between SPs with MT vs. SPs with RT), assuming a moderate effect (Khoury et al., 2013a,^2015^), a power of 0.8 and an alpha of 0.05 (Cohen, 1977) and the expectation 15 to 20% attrition rate. We will exclude participants who: (1) have a regular meditation practice; (2) have already participated in a formal mindfulness training (such as MBSR or a meditation retreat); or (3) had a social support skills training (e.g., counselors, psychologists, social workers, or other medical personnel).

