### 2.3. Randomization and allocation concealment

A total of 640 participants will be randomly divided into four equal groups (of 160 each) using a computer-based algorithm administered by a third party to ensure concealment. One group will be designated as SPs while the other three will be designated as SRs. Thus, for each SP, three dyads with different SRs will be formed using a computer algorithm to ensure randomization, i.e., (SP, SR1) to assess the quality of the dyadic interaction pre-training, (SP, SR2), to assess the quality of the dyadic interaction post-training, and (SP, SR3) to assess the quality of the dyadic interaction at follow-up (total of 3 × 160 = 480 dyads; see Figure 2). The experimental design, allocation procedure, and analyses are intended to minimize the effects of the dyad (i.e., unique combination of SP/SR in a dyad) vs. the SP and SR effects on the measured outcomes. In addition, according to the power analysis using Monte Carlo simulation (Schoemann et al., 2014), which is appropriate for dyadic research (Ledermann et al., 2022), 80 dyads per group should be sufficient (powered enough) to detect moderate effects (i.e., changes between baseline, post, and follow-up time points), and thus, beyond the variability between the dyads (e.g., personalities and other personal/interpersonal characteristics).

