### 2.5. Experimental procedure

#### 2.5.1. Experiment–Part I; pre-training

A total of 160 (SP, SR1) dyads will be invited to the lab. Upon arriving to the lab, members of each dyad will meet separately with two different research assistants (RAs). After signing a consent form, providing basic socio-demographic data, and filling-in the SDS, the SR will be asked to complete the FOCO (Gilbert et al., 2011), PANAS (Watson et al., 1988), and the MAAS-State (Brown and Ryan, 2003). Afterward, the SR will receive the 15-min mood induction while the SP will wait in a separate room doing an activity of their choice (e.g., reading popular magazines). Then, the SR will be asked to complete the PANAS and MAAS-State for a second time (as a check of the induction). Afterward, the SP and SR will be introduced to each other, the SR will be asked to discuss with the SP the event (which was part of the induction), and the SP will be asked to provide support to the SR as best they can during a 15-min videotaped interaction. The interaction will occur face-to-face, will be recoded, and the video will be rated by two trained graduate students according to the BOMDI (Cuperman and Ickes, 2009). Both the SP and SR will also be blind to the objectives of the study. Following the interaction, the SR will be asked again to complete the PANAS, MAAS-State, and the MEESS (Goldsmith et al., 2000). At the end of this part of the experiment, the SR will be debriefed about the study and its objectives.

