#### 2.5.2. Experiment–Part II; mindfulness/relaxation training

SPs (total of 160) will be asked to complete measures of mindfulness, perceived stress, emotion regulation, empathy, compassion for others, active listening, perspective taking and interpersonal mindfulness. Then, they will be randomly and equally divided into two groups using a computer algorithm to ensure randomization and concealment. Half of the SPs (80) will receive the MT (MBSR-ld) and the other half will receive the RT. Participants in both groups will be asked to complete the daily logs during the 8 weeks. After the training, the same measures will be administered to the SPs.

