## 3. Data analyses strategies

To ensure data reliability, self-reported data will be inspected for normality and skewness and outliers will be eliminated. Interrater reliability for the behavior observation data will be computed. An interrater coefficient of 0.95 or above is expected.

To test H1.1, H2.1, and H3.1, we will perform a mixed (2 groups × 3 time-points) multivariate analysis of covariance (MANCOVA) controlling for social desirability (and for Fears of Compassion from Others for H3.1). MANOVA/MANCOVA allow to reduce Type-I errors (i.e., rejecting the null-hypothesis when it is true, correcting therefore for multiple comparisons) when testing changes in multiple dependent variables. To test H1.2, we will use a regression analysis. To test H2.2 and H3.2, we will use a path analysis. To test associations and meditation/moderation at baseline (Hbase), we will use correlations and PROCESS macro with 5,000 bootstrapped/bias-corrected confidence intervals (Hayes, 2018). Structural Equation Modeling (Klem, 2000) may be used as well if the power is sufficient.

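### Section 3 states no role for each provider's Part I interaction quality in the H2.2 path model, although using it would strengthen the S-ART-to-quality path without new data

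*Protocol article*

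**What the plan says.** **Hypothesis.** Section 1.3 (H2.2) says that the effect of mindfulness training (MT) on interaction quality "will be mediated by the increase on S-ART of the SPs at both times points". The mediator is therefore a change. The outcome is quality at post-training and at follow-up, and it is not worded as a change. Objective O2.2 in the Introduction lists the SP's self-awareness, regulation and transcendence as mediators without calling them increases.

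**Analysis.** Section 3 gives one sentence: "To test H2.2 and H3.2, we will use a path analysis". The same paragraph does name covariates for the MANCOVA: social desirability, plus fears of compassion for H3.1.

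**Data available.** Section 2.3 gives the purpose of the first dyad as "SP, SR1) to assess the quality of the dyadic interaction pre-training". Section 2.5.1 says "A total of 160 (SP, SR1) dyads will be invited to the lab". Randomisation to training comes afterwards (section 2.5.2): "Half of the SPs (80) will receive the MT (MBSR-ld) and the other half will receive the RT".

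**Expected baseline association.** Hbase in section 1.3 states: "At baseline, the S-ART measures of the SPs will be associated with the quality of SP-SR interactions".

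**The concern.** Randomisation protects the path from training to S-ART. It does not protect the path from S-ART to interaction quality. Hbase expects those two to be related before anyone is trained, which suggests that some SPs bring a supportive skill feeding both. The BOMDI scores the SP's own behaviour, so that skill plausibly carries from Part I into Parts III and IV. Part I quality is the most direct measure of it, yet section 3 assigns it no role in H2.2.

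Two things could be at stake. If the mediator is a change and the outcome is raw post-training quality, real mediation may be missed. If the mediator is entered as a post-training level, part of the pre-existing association may be read as an effect of training. The point concerns the baseline of the outcome, not only the baseline of the mediator.

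**Working it through.** **1. The plan's sample size.** Inputs from section 2.1 are "assuming a moderate effect" and "a power of 0.8 and an alpha of 0.05 (Cohen, 1977) and the expectation 15 to 20% attrition rate". I take d = 0.5 and a two-sided test, since neither is stated. n = 2(1.96 + 0.842)²/0.5² = 62.8, so 63 per group. With 20% attrition, 63/0.8 = 78.75, so 79; the t-based 64/0.8 gives 80. With 15%, 63/0.85 gives 75. The stated 80 per group reproduces and does not depend on this point. At 20% attrition, 160 × 0.8 = 128 SPs complete.

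**2. Model and assumptions (none given in the article).** U is stable skill, S is S-ART, Q is quality, and 0 and 1 mark Part I and Part III.
- S0 = us·U + T + e0
- S1 = us·U + T + 0.5·arm + e1
- Q0 = uq·U + b·S0 + f0
- Q1 = uq·U + b·S1 + f1

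Here us = 0.4–0.5, uq = 0.5–0.6, var(T) = 0.25, within-arm var(S) = 1 and var(f) = 1 − uq². The S-ART retest correlation is r = us² + 0.25 = 0.41–0.50. The Part I to Part III quality correlation is 0.25–0.45. Mediation is declared when both paths are positive and significant at two-sided 5%.

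**3. H2.2 as worded, true b = 0.25.** Worked for us = 0.4, uq = 0.5, n = 160.
- var(e) = 0.59, so var(ΔS) = 1.18. Training to ΔS: z = 0.5/√(4 × 1.18/160) = 2.91, power 83%.
- *Without Q0:* cov(Q1, ΔS) = 0.25 × 0.59 = 0.1475 and slope = 0.1475/1.18 = 0.125. var(Q1) = 1 + 2(0.5)(0.25)(0.4) + 0.25² = 1.1625, residual 1.144. SE = √(1.144/(160 × 1.18)) = 0.078, z = 1.61, power 36%. Both paths: 0.36 × 0.83 = 30%.
- *With Q0 as covariate:* cov(Q0, ΔS) = −0.1475 and cov(Q0, Q1) = 0.376. Slope = 0.1475(1.1625 + 0.376)/(1.18 × 1.1625 − 0.1475²) = 0.168. Residual variance 1.008, SE = 0.074, z = 2.28, power 63%. Both paths: 52%.
- *Change in quality:* slope 0.25, residual variance 2(1 − 0.25) = 1.5, SE = 0.089, z = 2.80, power 80%. Both paths: 66%.

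Simulation over the assumed range agrees:

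| SPs | No Part I quality | Part I covariate | Change in quality |
|---|---|---|---|
| 160 | 26–30% | 51–58% | 66–70% |
| 128 | 19–21% | 37–44% | 52% (worked case only, same formula) |

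**4. Where the gain comes from.** If only the SE fell to 0.074 and the slope stayed at 0.125, z would be 1.70 and joint power about 33%. So noise removal gives about 3 of the 22 points. The rest is partial recovery of a slope that is halved when a change mediator is paired with a raw outcome. For noise alone on the total effect (64 completers per group, d = 0.5, residual variance 1 − ρ²), power moves from 80.7% to 81.1% at ρ = 0.1, 84.3% at 0.3, 90.4% at 0.5 and 97.7% at 0.7.

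**5. False mediation, true b = 0.**
- *Mediator as increase:* U cancels in ΔS. The rate is about 2% with or without Q0 (0.025 × 0.83 = 2%).
- *Post-training level adjusted for S0:* the fitted slope is uq·us/(1 + r), from 0.2/1.41 = 0.14 to 0.3/1.5 = 0.20, against a true zero. With p = uq·us, adding Q0 makes it p(1 − uq²)/(1 + r − 2p²), from 0.15/1.33 = 0.11 to 0.192/1.32 = 0.145. Simulated false mediation at n = 160 is 36–61% without Q0 and 24–37% with it; at n = 128 it is 28–46% and 20–28%.
- *Level without baseline S-ART:* 63–85% without Q0 and 46–70% with it, n = 160.
- *Increase, with skill also predicting the S-ART gain (assumed loading 0.2):* false S-ART-to-quality findings of 28% without Q0 and 18% with it, 128 completers.

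**The case against.** The strongest reply is that the article does not say the model leaves Part I quality out. One sentence in a condensed paper lists no paths or covariates, and such detail commonly sits in a fuller document. Nearby text also leans towards using baseline. H3.2, covered by the same sentence, has an increase in quality as its mediator, which needs an earlier quality score. H2.1 is tested over three time points. APIM-M is named for the dyadic data, with power stated for changes that include baseline. This stands: a reader might infer that the plan excludes Part I quality, and the documents do not support that. They also do not say that it enters H2.2.

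A reader might further infer that prior skill biases H2.2 as written. It does not under stable additive skill, because the mediator is an increase and skill cancels. The high false-mediation rates need a level mediator, for which only O2.2's looser wording leaves room. Nor can prior skill confound the training-to-S-ART path or the total effect beyond chance imbalance, since training is allocated after Part I.

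It is also fair that much of the power gain reflects the pairing of a change mediator with a raw outcome, and that the gain may be small where a different support receiver (SR) sits in each dyad. What remains is that section 3 does specify covariates for other hypotheses, and that the one for this non-randomised path is collected but unassigned.

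**Conclusion.** The point holds as a gap in the stated H2.2 model, not as a demonstrated wrong analysis. As H2.2 is worded, omitting Part I quality loses power on the S-ART-to-quality path. Under the assumed loadings, using it takes power from 26–30% to 51–58% as a covariate, or to 66–70% through change in quality, with 160 SPs. It prevents no false mediation in that form unless skill also predicts the S-ART gain. If the mediator is entered as a level, Part I quality also reduces inflated mediation but does not remove it, because one dyad with a different SR is a noisy measure of skill.

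Every size depends on loadings and on a Part I to Part III correlation that the article does not report. Rescaling quality to unit variance, for instance, gives 30–36% without and 63–73% with the covariate. The gain is likely smaller for the MEESS, which a different SR rates each time, than for the BOMDI.

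**What to change.** Add to section 3 that each H2.2 path model (BOMDI and MEESS, at post-training and at follow-up) keeps the mediator as change from baseline S-ART. Each model should also use the same SP's Part I value of that quality measure, either as a covariate in both the mediator and the outcome equation or by modelling change in quality.

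The choice should be fixed before the data are seen, because the two forms trade off. Change in quality restores the mediator slope in the working above. For the training contrast, however, its variance is 2(1 − ρ) against 1 − ρ² with the covariate: at ρ = 0.3 that is 1.4 against 0.91, where ignoring baseline gives 1.

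The cost is one sentence of wording and, in the covariate form, one degree of freedom per equation. No new data are needed, since Part I is already scored before training is allocated.

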Outcome (variable)	Variable type	Dyadic interaction Part I, III and IV of the experiment				Mindfulness/Relaxation training Part II of the experiment			
		Pre-induction	Post-induction	During interaction	Post-interaction	Pre-training	During training	Post-training	3-months follow-up
Trait mindfulness	Dep/Cntrl					SP		SP	SP
Perceived stress	Dependent					SP		SP	SP
Emotional regulation	Dependent					SP		SP	SP
Empathy	Dependent					SP		SP	SP
Compassion–Others	Dependent					SP		SP	SP
Active listening	Dependent					SP		SP	SP
Perspective taking	Dependent					SP		SP	SP
Interpersonal mindfulness	Dependent					SP		SP	SP
Behavior observation	Dependent			SP-SR					
Enacted social Support	Dependent				SR				
Adherence to practice	Control						SP		
Emotional experience	Cntrl/Dep.	SR	SR		SR				
State mindfulness	Dependent	SR	SR		SR				
Fears of compassion	Control	SR							
Social desirability	Control	SR				SP			

Dep, dependent; Cntrl, control; SP, support provider; SR, support receiver.

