Regarding the dyadic data, we will use the Actor-Partner-Interdependence-Model (APIM; Kenny and Judd, 1986; Kenny and Malloy, 1988; Griffin and Gonzalez, 1995; Kenny, 1996; Kenny et al., 2020) and APIM-M (M for mediation) as we cannot assume independence between the members of the dyad (Gonzalez and Griffin, 2012). APIM/M allows us to test the interactions between the SP and the SR scores on a given predictor (Kenny et al., 2020). To calculate power for the APIM/M, we used a Monte Carlo simulation (Schoemann et al., 2014), which is applicable for APIM/M (Ledermann et al., 2022). Results suggested that 80 dyads per group should be sufficient (powered enough) to detect moderate effects (i.e., changes between baseline, post, and follow-up time points) for an alpha of 0.05. In addition, if for some dependent variables, the power is insufficient to detect a change, we will use Bayesian Analysis (Fitzpatrick et al., 2016) instead of APIM/M as authors have previously recommended (Sagan and Kowalska-Musiał, 2009; Ledermann et al., 2022). All the statistical analyses will be conducted using R (R Core Team, 2021). If multiple statistical analyses (e.g., *post hoc* ANOVAs or *t*-tests) are to be conducted sequentially on the same set of dependent variables, the level of significance (alpha) will be divided by the number of tests (multiple comparisons correction) to reduce the risk of false positives (i.e., reducing Type-I errors).

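### The standard APIM/APIM-M in section 3 cannot be specified from the Table 1 measures, so its Monte Carlo power statement describes a model these data cannot support

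*Protocol article*

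**What the plan says.** Section 3 (Data analyses strategies) of the protocol article names the model: "Regarding the dyadic data, we will use the Actor-Partner-Interdependence-Model", together with its mediation extension. It gives two reasons. Members of a dyad cannot be taken as independent, and "APIM/M allows us to test the interactions between the SP and the SR scores on a given predictor".

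The same section ties a power claim to this model: "To calculate power for the APIM/M, we used a Monte Carlo simulation", followed by "Results suggested that 80 dyads per group should be sufficient (powered enough) to detect moderate effects" at alpha 0.05. Section 2.3 repeats the 80-dyad figure. In both places the effect is explained as change across the three assessment occasions. If power proves too low for some dependent variables, a Bayesian analysis is to take the place of APIM/M.

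Just before this, section 3 assigns H2.1 and H3.1 to a mixed 2 × 3 MANCOVA, H2.2 and H3.2 to path analysis, and Hbase to correlations and PROCESS. APIM/M is linked to no numbered hypothesis.

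Section 2.1 gives a separate sample-size rationale for the SP comparison, "assuming a moderate effect", with power 0.8, alpha 0.05 and 15 to 20% attrition.

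**The concern.** A standard APIM estimates two actor paths (each member's own predictor to own outcome) and two partner paths (each member's predictor to the other's outcome). It needs one predictor and one outcome measured on both members. In this trial the two members have different roles and complete different questionnaires, so the plan names a model that its own schedule may not be able to feed.

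Transfer from SP to SR is the central claim of the trial. If the named dyadic model cannot be fitted, something else will be reported under that name, or the method will be dropped without a statement of what replaces it. A power result for a model that cannot be fitted also gives no assurance about the analyses that will be run.

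**Working it through.** **Step 1. Who supplies each variable.** Table 1 has 15 rows. I read them with sections 2.4 and 2.5.

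| Source | Variables | Rows |
|---|---|---|
| SP only, dependent | trait mindfulness, stress, emotion regulation, empathy, compassion, active listening, perspective taking, interpersonal mindfulness | 8 |
| SP only, control | adherence to practice | 1 |
| SR only | enacted support (MEESS), PANAS, MAAS-State, fears of compassion (FOCO) | 4 |
| One score per dyad | behaviour observation (BOMDI) | 1 |
| Both members | social desirability, a control | 1 |

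The total is 8 + 1 + 4 + 1 + 1 = 15.

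Two rows need care. The BOMDI cell is marked for SP and SR together, but section 2.4 says that the instrument codes the SP's behaviour, so it gives one score and not a pair. The row "State mindfulness" is entered for the SR only; the SP completes the trait form, which is a different construct. Sociodemographics (section 2.4) also come from both members but are not in Table 1.

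The procedures agree. In Part I the SP waits during the induction, and only the SR completes scales after the interaction. Parts III and IV follow the same pattern.

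**Step 2. What can be formed.** The number of dependent variables measured on both members is 0. The number of substantive predictors measured on both (S-ART, affect, state mindfulness, interaction quality) is also 0. The two-outcome model therefore cannot be specified for any study outcome. What remains is one-sided: an SP score (a partner-type path) and an SR score such as FOCO (an actor-type path) predicting an SR outcome.

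**Step 3. The non-independence rationale.** With each outcome observed on one member, there is no SP–SR outcome correlation to model. The dependence that the design does create is of two other kinds:
- Three dyads share one SP (section 2.3).
- SPs are trained in groups of 6 to 8, six groups a year for four years (section 2.6): 6 × 4 = 24 groups, or 12 per arm.

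An APIM for separate dyads represents neither.

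**Step 4. The figure of 80.** The Monte Carlo result can be neither reproduced nor refuted, because no path coefficients, within-dyad correlation or attained power are given. The section 2.1 calculation can be checked if the moderate effect is taken as d = 0.5, two-sided (my assumption; no number is stated):
- Normal approximation: n = 2(1.960 + 0.842)²/0.5² = 62.8, so 63 per arm. The t-based value is 64.
- With 20% attrition: 64/0.80 = 80.
- With 15% attrition: 64/0.85 = 75.3, so 76.
- Power by t test: 0.88 at 80 per arm, 0.83 at 68 (80 × 0.85) and 0.80 at 64 (80 × 0.80).

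So 80 per arm stands as a plain two-group comparison.

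**Step 5. Illustration for models that can be fitted.** The effect sizes here are assumptions, not the plan's. For a single SP-to-SR correlation, power ≈ Φ(atanh(r)·√(n − 3) − 1.96):

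| r | n = 64 | n = 68 | n = 80 | n = 128 | n = 160 |
|---|---|---|---|---|---|
| 0.3 | 0.68 | 0.70 | 0.775 | 0.93 | 0.97 |
| 0.2 | 0.35 | 0.37 | 0.43 | 0.62 | 0.72 |

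The columns 128 and 160 pool both arms. For a simple mediation (d = 0.5 from arm to mediator, b = 0.3 from mediator to outcome, joint significance, 4,000 simulated trials), power is about 0.86 at 80 per group and 0.75 at 64. None of these allows for training-group clustering. Whether 80 per group is enough thus depends on which path is meant, whether the arms are pooled, and attrition.

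**The case against.** The strongest reply is that little depends on APIM. Every hypothesis under O2, O3 and the baseline objective already has a named method in section 3, and each can be specified from the scheduled measures. That stands. A reader might infer that the dyadic analyses for O2 and O3 cannot be run at all; the documents do not support this.

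Three further limits also stand:
- **Shared variables exist.** Social desirability and sociodemographics come from both members, so it is wrong to say that nothing is shared. But they are controls or background, not the predictors or outcomes that the model is meant to relate.
- **The sample size is not left without support.** A reader might infer that 80 per arm has no basis, but section 2.1 yields it independently (given d = 0.5). The simulation inputs may also sit in a fuller document.
- **Section 2.3 does not promise to separate SR effects from dyad effects.** It speaks of minimising dyad effects. That each SR takes part in one dyad, so that the two are confounded, does not contradict it.

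The three dyads per SP can also be handled in the mixed MANCOVA if the SP is the repeated unit.

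The reply does not rescue the APIM text. Model and schedule are both stated in the article and do not fit each other. A fuller document could supply simulation inputs, but it would have to change the model or the measures to reconcile the two.

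**Conclusion.** The point holds in a limited form. The standard APIM/APIM-M cannot be specified for any study outcome, because 0 dependent variables and 0 substantive predictors are measured on both members. The stated test of SP and SR scores on a common predictor has nothing to act on, and the 80-dyad Monte Carlo statement describes a model that these data cannot support. Only that analysis and that power justification fall. The MANCOVA and path analyses remain, and so does 80 per arm as a two-group sample size.

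The conclusion rests on the usual definition of APIM (predictor and outcome from both members) and on Table 1 and section 2.5 being the full schedule. The support for 80 per arm rests on reading the moderate effect as d = 0.5, two-sided.

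**What to change.** 1. In section 3, replace APIM/APIM-M with a one-directional path model that extends the path analysis already planned for H2.2 and H3.2: SP arm → SP S-ART measures → interaction quality → SR state, with the SR's FOCO as moderator. Make the SP the clustering unit across its three dyads, and include a training-group effect.
2. Reword the Bayesian fallback so that it refers to this model, since a change of estimation method does not supply the missing paired scores.
3. In sections 2.3 and 3, rerun the Monte Carlo power for this model and restate the result with its assumed path sizes, clustering and attrition, or withdraw the statement. The section 2.1 calculation can stay.

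The cost is an analysis-section rewrite and one new simulation. No new data are needed. Keeping a true APIM would instead require the same substantive measures from both members, which changes the schedule.

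### For the dyadic outcomes, an undefined finding of insufficient power replaces the planned APIM/APIM-M with Bayesian analysis, outcome by outcome, which invites a results-dependent choice of method

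*Protocol article*

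**What the plan says.** Section 3 (Data analyses strategies) assigns the dyadic data to APIM and APIM-M because the two members of a dyad cannot be treated as independent. It cites a Monte Carlo power calculation at an alpha of 0.05 and concludes that "80 dyads per group should be sufficient (powered enough) to detect moderate effects". The next sentence says that "if for some dependent variables, the power is insufficient to detect a change, we will use Bayesian Analysis", and that this is done "instead of APIM/M as authors have previously recommended".

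Section 2.1 (Participants) gives the planning basis for the comparison of support providers (SPs) between arms: "assuming a moderate effect", "a power of 0.8 and an alpha of 0.05", and "the expectation 15 to 20% attrition rate". Section 2.5.2 allocates 80 SPs to each training. Neither section gives a planning effect for any individual dependent variable.

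**The concern.** The sample size is fixed and planning power has already been declared adequate. A rule that then finds power lacking for particular variables needs information that separates one variable from another, and the article states none in advance. The natural source is the data: an estimate smaller than hoped, a variance larger than hoped, or a p-value above 0.05. Used that way, the rule changes the inferential framework for exactly those outcomes whose results are weak.

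The replacement does not solve the stated problem either. With a weak prior, the posterior holds the same information as the likelihood. With an informative prior, the prior makes the difference. Dyadic outcomes would then be judged by different standards depending on how they turned out. The alpha-division rule at the end of section 3 is framed in terms of significance levels and does not say how a Bayesian replacement counts.

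**Working it through.** **1. Is the planned size adequate on its own terms?** Inputs: alpha 0.05 (two-sided assumed), power 0.80, 80 per arm, attrition 15 to 20% (sections 2.1 and 2.5.2). The article gives no number for a moderate effect; d = 0.5 is assumed.

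- Normal approximation: n = 2(1.96 + 0.842)²/0.5² = 62.8, so 63 per arm. The exact t calculation gives 64.
- Allowing for attrition: 64/0.85 = 75.3, so 76; 64/0.80 = 80. The planned 80 per group is reproduced.

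This is the two-group calculation of section 2.1. The APIM/M simulation cannot be rerun because its inputs are not in the article.

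**2. Which outcomes could be short of power?** Exact t power per arm size (80 × 0.85 = 68; 80 × 0.80 = 64):

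| True effect (assumed) | n = 80 | n = 68 | n = 64 |
|---|---|---|---|
| d = 0.5 | 0.88 | 0.83 | 0.80 |
| d = 0.4 | 0.71 | 0.64 | 0.61 |
| d = 0.3 | 0.47 | 0.41 | 0.39 |

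Expected attrition alone leaves power at about 0.80 or more at d = 0.5. Insufficiency arises mainly where the effect is smaller than planned. If that is judged on observed effects, the rule picks out the weak results.

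**3. What could the switch do to the false-positive rate?** Assume that a non-significant result (|z| ≤ 1.96) triggers the switch. A false claim then occurs if |z| > 1.96, or if |z| ≤ 1.96 and the Bayesian criterion is met. The null z is standard normal, with SE = √(2/n) on the d scale. This is a simple two-mean model, not an APIM, and all priors and criteria are assumptions.

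- *Zero-centred normal prior, 95% credible interval excluding zero.* The posterior mean divided by its SD equals √w × z with w < 1, so the criterion needs |z| > 1.96/√w, which is stricter than 1.96. Nothing is added: **5.0%**.
- *Flat prior, posterior probability of benefit above 0.95.* The criterion is z > 1.645. Total: 0.050 + 0.025 = **7.5%**. In the hoped-for direction the rate goes from 2.5% to 5.0%. With a zero-centred prior of SD 0.5 the total is 6.5 to 6.7%.
- *Prior N(0.5, 0.25²), 95% credible interval above zero, n = 64.* The prior precision is 1/0.0625 = 16 and the data precision is 64/2 = 32. The posterior SD is 1/√48 = 0.144. The criterion is (8 + 32d)/48 > 1.96 × 0.144 = 0.283, so d > 0.174. With SE = 0.177 this is z > 0.99, which has probability 16.2%. Adding the lower tail of 2.5% gives **18.7%**. At n = 80 the same steps give 17.1%.
- *Prior N(0.25, 0.25²)*: about 7%.
- *Bayes factor, prior SD 0.5*: above 3 gives 5.0%; above 1 gives 10 to 12%.

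A simulation of one million null z-values agrees with these figures.

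**4. A different trigger.** Suppose instead that observed power below 0.80 triggers the switch, that is |z| < 1.96 + 0.84 = 2.80, and only the Bayesian criterion then counts. The flat-prior directional rule gives P(z > 1.645) + P(z < −2.80) = 0.050 + 0.003 = 5.3%. The N(0.5, 0.25²) prior at n = 64 gives 0.162 + 0.003 = 16.5%. The prior therefore matters more than the exact trigger.

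**The case against.** The best defence is that the article never says power will be judged from the results. Power for a smaller anticipated effect can be computed with no outcome data, as step 2 shows. Achieved sample size and blinded pooled variances are also possible triggers. This stands: a reader might infer that the plan prescribes a post hoc power check, but the text is silent on timing. What remains is that the rule as written permits one, and that the article states no outcome-specific basis for doing otherwise.

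Secondly, the Bayesian analysis is a replacement. A reader might infer that every failed test gets a second one; the text does not say so. Step 3 models a replacement whose trigger is non-significance, and that trigger is an assumption.

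Thirdly, a reader might extend the point to the whole analysis. The documents do not support that. The substitution is tied to APIM/M, and section 3 attaches no Bayesian fallback to the MANCOVA or regression analyses. Nor does the sentence that structural equation modelling "may be used as well if the power is sufficient" belong here: it is an optional addition and replaces nothing.

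Finally, the fallback rests on cited methodological sources that are not at hand, and priors, thresholds and decision rules may properly sit in an analysis plan. Their absence is not the complaint. Supplying them would not by itself remove an outcome-by-outcome substitution that the article does state.

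**Conclusion.** The point holds for the dyadic outcomes analysed with APIM/APIM-M. The article declares the design adequately powered and then makes the choice of framework for each outcome depend on an undefined lack of power, a lack that the replacement does not cure without an informative prior.

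Inflation of the type I error is possible but not established. If non-significance triggers the switch, the per-outcome rate lies between 5% and about 19%, depending on a prior and decision rule that the article does not fix. It would be too strong to say that alpha control is lost, or that the upper figure is expected: no part of the article proposes a prior centred on d = 0.5. The case for change rests on the rule itself and on the fact that removing it costs almost nothing. It is a change that should be made.

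**What to change.** Delete the power-triggered substitution from section 3. State that the pre-specified APIM/M estimate and its 95% CI will be reported for every dyadic outcome whatever its power, and that the conclusion rests on that model. If Bayesian results are wanted, run them for all APIM/M outcomes as a labelled sensitivity analysis, with priors and decision rule fixed before any outcome data are seen.

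The cost is a rewritten sentence or two, with no extra participants or data. The drawback is that some outcomes will be reported as inconclusive.
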